**Fig. 1 Fig1:**
[figure not shown]
Flow chart of the GAME-S study

### Recruitment

For privacy purposes, the medical records in each service organisation will be screened by the clinical staff to determine the eligibility of patients to participate in the study. To ensure that patients have the capacity to make the decision to participate or not, an extended informed consent process will be used [36]. Eligible participants will first receive a short leaflet about the study from the staff or during a short information session organised for the participants to consider their availability. If an eligible patient shows interest, more detailed written and oral information will be given. It will be ensured that a patient understands the information and they will have the opportunity to ask any questions. If a patient is willing to participate in the study, they will sign an informed consent form. To ensure accuracy of the written information to be provided to subjects, its content will be revised whenever new information relevant to the subject’s consent becomes available. Prior to participation in the trial, the study participants will receive a copy of the signed and dated written informed consent form and any other written information provided to the subjects. If any updates occur, the participant will receive a copy of the signed and dated consent form updates and a copy of any amendments to the written information provided to subjects during their participation in the trial.

After signing the informed consent form, background information of each respondent, their Intelligence Quotient (IQ, if available in medical records) and Mini Mental State Examination (MMSE) will be collected [37]. Their medication dosages (chlorpromazine equivalence) will also be collected as medications currently used in schizophrenia may affect the response to cognitive training strategies [9, 37]. A simple practical test to assess the participants’ computer skills will be carried out (starting up a computer, using a mouse). If any doubts of computer use arise, our intervention is long enough (12 weeks) for participants to learn basic computer and gaming skills. The recruitment will end as soon as the planned total numbers of participants are reached for the analysis.

### Randomisation, allocation concealment and blinding (masking)

After baseline data collection, the trial manager will be notified of new participants. Each participant will be allocated to one of the three arms based on a list of computer-generated random numbers provided by an external clinical trial randomisation service (blocks of 6 consecutive patients, a 1:1:1 ratio). Allocation will be masked to the trial statistician, but it cannot be masked to the research assistants (RAs) who will supervise the gaming sessions and collect follow-up outcome data, or from the study unit staff who will work with the patients. Furthermore, a sub-sample of 150 participants will be recruited for EEG analysis, and 126 participants from our total sample will be randomly selected and assigned to neuroimaging assessment at baseline (fMRI). Again, the participants for neuroimaging assessment will be allocated based on a separate list of computer-generated random numbers provided by an external clinical trial randomisation service (blocks of 6 consecutive patients, a 1:1:1 ratio). The trial manager will inform the RAs the identities of participants allocated to fMRI assessment.

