### Study setting and participant characteristics

The data collection, subject recruitment and gaming will be carried out in outpatient services (e.g., outpatient psychiatric units, day hospitals, residential care homes). Specific inclusion criteria mandate that patients should have a formal diagnosis of schizophrenia spectrum disorder (Diagnostic and Statistical Manual of Mental Disorders, fifth edition, DSM-5), and be between 18 and 60 years old. We will intentionally recruit people who are non-active, less-experienced gamers [19]. Participants will be required to be able to speak Cantonese, be able to participate based on their own free will and have the ability to provide written informed consent. Participants should have a cognitive status deemed suitable for study participation based on ‘the judgement standard’, i.e., be approved by the staff responsible of the treatment based on their clinical expertise.

The exclusion criteria are: 1) meeting the diagnostic criteria for a current major depressive, manic or hypomanic episode (DSM-5), or mental retardation, 2) having severe visual impairment, 3) being an active gamer (i.e. gaming > 5 h/week [17]), 4) displaying a lack of ability to decide one’s own participation, 5) substance abuse (other than nicotine dependence), 6) head injury, hemiplegia, or other neurological disorder, 7) electroconvulsive therapy (ECT) in the past six months, 8) having a lack of Magnetic Resonance Imaging (MRI) compatibility (e.g., cardiac pacemakers, metallic implants, restless behaviour, claustrophobia), and 9) pregnancy.

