## Study status

Patient recruitment is ongoing.

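### A single fixed block size of 6, published during recruitment, makes allocation more predictable than it need be to staff who influence entry; by how much depends on list arrangements the article does not give.

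*Protocol article*

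**What the plan says.** The Protocol article, under Randomisation, allocation concealment and blinding (masking), sets the main-trial method: "Each participant will be allocated to one of the three arms based on a list of computer-generated random numbers". An external randomisation service supplies the list, in "blocks of 6 consecutive patients, a 1:1:1 ratio". With three arms, that is two patients per arm in every block. No variation in block size and no stratification by site is stated. Allocation follows baseline assessment: "After baseline data collection, the trial manager will be notified of new participants".

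On masking, the same section says of allocation that "it cannot be masked to the research assistants (RAs) who will supervise the gaming sessions and collect follow-up outcome data". Site personnel are named as unmasked too, since the sentence then adds "or from the study unit staff who will work with the patients".

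Entry is in the hands of site staff. Under Recruitment, patients' files at each service "will be screened by the clinical staff to determine the eligibility of patients to participate in the study". Under Study setting and participant characteristics, a patient's cognitive suitability must "be approved by the staff responsible of the treatment based on their clinical expertise". The settings include outpatient psychiatric units, day hospitals and residential care homes.

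The Study status section reads: "Patient recruitment is ongoing".

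**The concern.** Concealment has two parts: hiding the list, and preventing anyone from working out the next entry from the entries already revealed. The external service achieves the first. A fixed and known block size weakens the second, because once an arm has its two places filled it cannot recur until the next block starts.

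This matters when the people who learn past allocations can also affect who enters, or when. Here unit staff know their own patients' arms, site clinical staff screen, and treating staff apply a criterion that rests on judgement. Someone who suspects the next arm could hold back or bring forward an approach to a particular patient. Arms could then differ in motivation, rapport or expected engagement, in a trial where the interventions differ visibly and one arm receives no gaming at all.

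**Working it through.** The article gives no predictability figure, so there is none to reproduce. The inputs are the block size (6), the three arms and the 1:1:1 ratio, all from the Randomisation section.

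**Step 1: upper bound, full view of the list.** A block has 6!/(2!·2!·2!) = 90 orderings. Assume an observer who sees every allocation in order and knows where blocks start.

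| Position | Next arm certain | At least one arm ruled out | Best guess right |
|---|---|---|---|
| 1 | 0 | 0 | 1/3 = 0.333 |
| 2 | 0 | 0 | 2/5 = 0.400 |
| 3 | 0 | 0.2 | 0.500 |
| 4 | 0 | 0.6 | 0.4 × 1/3 + 0.6 × 2/3 = 0.533 |
| 5 | 18/90 = 0.2 | 1 | 0.2 × 1 + 0.8 × 1/2 = 0.600 |
| 6 | 1 | 1 | 1.000 |
| Sum | 1.2 | 2.8 | 3.367 |
| Sum ÷ 6 | 20.0% | 46.7% | 56.1% |

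Position 3: the first two patients share an arm with probability 1/5. Position 4: the first three are all different with probability 4/5 × 2/4 = 0.4; otherwise (0.6) one arm is full. Position 5: the last two places belong to one arm in 3 × 4!/(2!·2!) = 18 orderings.

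**Step 2: partial view, one common list.** Suppose a unit recruits a share p of patients, units are randomly interleaved, and staff see only their own patients but are generously assumed to know the block boundaries. The next arm is certain only if all four patients who fill the other two arms came from that unit, which has probability p⁴. The certain share of the unit's own allocations is therefore (1 × p⁴ + 0.2 × p⁴)/6 = 0.2 × p⁴.

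| Share p | 0.2 × p⁴ |
|---|---|
| 1 (own list, or full view) | 20% |
| 0.8 | 8.2% |
| 1/2 | 1.25% |
| 1/3 | 0.25% |
| 1/5 | 0.03% |

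The article gives neither the number of units nor their shares, so p is an assumption and the table shows the range.

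**Step 3: effect of the change, again with a full view.** Larger fixed blocks help only moderately: certainty is 14.3% for blocks of 9 and 11.1% for blocks of 12. In a simulation of 300 lists of 234, for an observer who knows the set of sizes but not their order, certainty is about 5.1% for {6, 9} and 2.5% for {6, 9, 12}. The best guess falls less, from 56.1% to 52.9% for {6, 9, 12}. Varying the size mainly removes certainty; it does not bring guessing down to the 33% of chance.

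**The case against.** The strongest reply is that nobody in the article is shown to have the view that the 20% requires. Masking is said to be impossible for assistants who supervise sessions and for staff who work with the patients. That does not mean any unit learns other units' allocations, their order or where a block begins. The staff who screen belong to individual organisations and, on the natural reading of one common list, see only a fraction of it. This stands, and Step 2 shows how sharply it reduces the figure. It does not settle the matter: the article describes neither how assistants are spread over sites nor whether lists are held per unit, and either could restore most of the 20%.

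A reader might infer that about 47 participants are exposed (0.20 × 234 = 46.8, with 234 from the Abstract). The documents do not support that count. Registration was in April 2017 and publication in January 2021. Publication cannot have revealed earlier allocations, nothing says staff knew the block size before then, and the number still to be randomised is not given.

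A reader might also infer that such bias is beyond any repair in analysis. That goes too far. Baseline outcomes are collected before allocation, the main model tests group-by-time terms against baseline, and baseline variables that differ become covariates (Data analysis, Cognitive and clinical outcomes). Selection on measured status is partly addressed; selection on unmeasured factors is not.

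Finally, blocks of 6 are not an error or a contradiction, and external generation after baseline is sound. That is fair. The weakness lies in the combination of fixed size, publication during recruitment, unmasked staff and discretionary entry.

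**Conclusion.** The point holds as an avoidable weakness in concealment, not as evidence that bias has occurred. The size is a range. At the top, 20% of allocations are certain and the best guess is right 56% of the time against 33% by chance, for someone with the full sequence and the block boundaries. For a unit that sees only its own share of a common list, certainty is about 0.2 × p⁴: 1.25% at one half and well under 1% at one third or less, assuming random interleaving. The article does not allow a choice between these.

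The neuroimaging list carries the same block wording, and a reader might extend the point to it. No harm is shown there: that list selects participants for scanning, and the three-arm figures above are not shown to apply to it.

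The change is worth making because it is cheap and the mechanism cannot be ruled out from the text.

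**What to change.** Ask the existing external service to generate the remaining main-trial allocations with randomly varying block sizes in multiples of 3, for example 6, 9 and 12. Neither the sizes nor their order should be disclosed to trial or unit staff. Replace the exact block size in any document that staff can see with a statement that sizes vary and are held by the service.

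The cost is one request and one protocol sentence. If recruitment stops mid-block, the largest possible difference between two arms within the open block is one third of its size: 4 patients for a block of 12, against 2 for a block of 6. An incomplete block of 6 at the changeover could add up to 2 more. Allocations already made stay as they are.

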### Interventions

Participants will be allocated into three groups: 1) cognitive training with computerised exercises (G1, CogniFit, *N*=78), 2) entertainment video gaming (G2, Entertainment Gaming, *N*=78), and 3) treatment as usual (*N*=78). CogniFit and entertainment games (SIMS 4) represent two distinct gaming genres: CogniFit is a cognitive training package with computerised exercises aiming to improve cognitive abilities based on a personalised brain training regimen. SIMS 4 is a pure entertainment game without any known health impact. The administration of both interventions will include 60 pre-scheduled gaming sessions [38] at the study settings as part of the normal day programme, lasting from 45 to 60 min each, at least 5 days/week [17], 60 h in total. The gaming schedule can also be tailored based on the participants’ needs (working, studying, family issues) as long as the gaming hours are in line with the total hours planned. Individual gaming sessions on separate computers will be conducted in small groups (about 3–6 per group) and closely monitored by the trained research assistant. Monitoring of gaming sessions is crucial to ensure intervention fidelity. This was exemplified in our feasibility study, which showed that, out of all possible 60 pre-scheduled sessions, 97% of sessions were realised as planned, and all participants enjoyed gaming. Gaming hours (diaries, automatic gaming logs) for each gaming session will be recorded to provide evidence of the intervention fidelity; a minimum of 50 gaming hours will be acquired to ensure observable neuroplasticity after gaming [19]. To report any negative side effects of gaming (e.g., tiredness of eyes), feedback and any concerns will be reported in a gaming diary after each gaming session [39].

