### Power analysis and sample size

We have calculated the sample size based on the primary outcome as follows: (1) the number of actual pairwise tests to be made for the efficacy of the primary outcome and (2) the two-level modelling approach in the final data analysis, in which the type I error has been adjusted. The statistical efficiency will be ensured using the multivariate analysis of variance (MANOVA) method for multiple group comparison. First, given that video gaming is a fairly novel strategy, we will base the sample size calculation (a priori) [32] on a cognitive-efficacy meta-analysis for patients with schizophrenia [33] showing an overall effect size (ES, Cohen’s *d*) of 0.58 on verbal working memory (a primary outcome). Based on our hypothesis, the primary endpoints will be the effects on verbal working memory after 3 and 6 months of cognitive training group (CogniFit), compared with the other two groups: cognitive training vs. entertainment gaming, cognitive training vs. non-gaming control group, and entertainment gaming vs. non-gaming control group. Four pairwise interactions between the contrast of the two comparisons and the two time points will be tested. For multiple comparison tests of four, for a type I error level of 5% (two-sided), an adjusted significant level should be α/2 = (1- (1–0.05)4) /2 = 0.01274 /2 = 0.0064, and the corresponding z score for a one-tailed test should be 2.49. Given the effect size 0.58, assuming equal sample size of the three groups, with a statistical power of 0.8 and α= 0.01274*,* we will require at least 198 subjects (66 per group at follow-up phase) by applying the equation, 2(Z1-β + Z1-α/2)2 / ES2. According to a meta-analysis [33], the total sample size in previous cognitive training studies was around 50 (range 10–138).

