In the main analysis, we will estimate and test efficacy of interventions on the primary and secondary outcomes. Based on the intention-to-treat principle, we will first assess intervention effects on the primary outcome, verbal working memory, by means of multilevel modelling analysis. A two-level model can be built with repeated time points at level 1, and patients at level 2. Two indicator variables, G2 and G3, will be included in the fixed part of the model to estimate and test mean differences between the cognitive training group with computerised exercises (G1) and the entertainment gaming group (G2), as well as between G1 and the non-gaming control group (G3). The baseline difference between G2 and G3 can be tested using a Ward test, based on the regression coefficient estimates of the two indicators. For changes in the outcome over time, two more indicators, variables T2 and T3, in contrast to the baseline time point, T1, will be included in the fixed part of the model to estimate changes from baseline to 3 months, and from baseline to 6 months. To assess the effects of interventions over time, interaction terms between the treatment group indicators, G2 and G3, and time indicators, T2 and T3, will be included in the fixed part of the model. The significantly different demographics between groups identified in the first step of the analysis and other possible confounders will be adjusted by including them in the main effect model. The within-patient random effects of the outcome measurements will naturally be taken into account by the level two variance in the model. A pairwise comparison and other hypotheses on the intervention effects can be tested using a generalised Ward test with an adequate degree of freedom from the modelling analysis. This analysis approach has two main advantages: a statistically highly efficiency and taking missing data into account. The effects of interventions on other secondary outcome measures, normally distributed and measured at three time points, such as patients’ cognitive and social functioning, experience of pleasure, and self-efficacy, will be analysed using the same model, but a separate model for each outcome. A multilevel logistic model will be used for outcomes in binary form, and multilevel multinomial models will be used for ordinal or nominal outcomes. For outcomes measured at two time points only, such as neurocognitive outcomes, the model will have only one time indicator with two interaction terms to test the efficacy of cognitive training with computerised exercises three months into the trial.

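### Both gaming arms train in small supervised groups, but the primary model stops at the patient and has no term for training group, research assistant or site

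*Protocol article*

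**What the plan says.** **Delivery.** The Interventions section states for both gaming arms: "Individual gaming sessions on separate computers will be conducted in small groups (about 3–6 per group) and closely monitored by the trained research assistant". There are 60 scheduled sessions within the normal day programme, and the schedule may be tailored to the participant. The sections on the two gaming interventions have an RA at every session for support. The treatment-as-usual section offers no gaming, so that arm has no training groups.

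**Settings and assessors.** Recruitment and gaming "will be carried out in outpatient services (e.g., outpatient psychiatric units, day hospitals, residential care homes", in the words of Study setting and participant characteristics. The Randomisation section says that the RAs who supervise gaming also collect follow-up outcome data and cannot be masked.

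**Allocation.** "Each participant will be allocated to one of the three arms based on a list of computer-generated random numbers", in blocks of 6 at 1:1:1. No stratification factor is mentioned.

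**Analysis.** Data analysis, Cognitive and clinical outcomes: "A two-level model can be built with repeated time points at level 1, and patients at level 2". The fixed part holds two arm indicators, two time indicators and their interactions, plus demographics that differ at baseline and other possible confounders. Site, RA and training group are not named.

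**Sample size.** "Given the effect size 0.58, assuming equal sample size of the three groups", the Power analysis section applies the usual formula for two independent means, without a design effect.

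**The concern.** People who train in the same room, on the same timetable and with the same RA for up to 60 hours share influences on how much they improve. If that RA also tests them, they share measurement influences too. A model whose highest level is the patient treats their changes as independent. If change is positively correlated within single-arm groups, the standard errors of the group-by-time contrasts are too small, and those contrasts carry the primary hypothesis.

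The shared source exists by design in two arms of three. It can therefore affect CogniFit against SIMS 4 on both sides of the contrast, and CogniFit against treatment as usual on one side only.

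Site raises a related point. The primary test concerns differences in change over time. If site enters only as a main effect that is constant over time, it does not adjust those differences; a site-by-time term is needed for that.

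**Working it through.** **Step 1. Reproduce the plan's figure.** Inputs from Power analysis and sample size: overall error "for a type I error level of 5% (two-sided"), four tests, the adjusted level "0.01274 /2 = 0.0064" per tail, "with a statistical power of 0.8", and effect size 0.58.

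- Adjusted level: 1 − 0.95^(1/4) = 0.01274 two-sided, so z = 2.491; z for power 0.80 is 0.842.
- n per arm = 2 × (0.842 + 2.491)² / 0.58² = 66.03.

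This agrees with the stated 66 per arm (198 in total). It is reached with independent patients, so no allowance for clustering is built in.

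**Step 2. Variance factors.** Let m be the training group size and ρ the within-group correlation of change.

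- The article gives m as about 3 to 6; I take the midpoint, 4.5.
- The article does not give ρ; I assume 0.02 to 0.10.
- I also assume stable groups that contain one arm only, which the article does not state.

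For CogniFit vs SIMS 4 (both arms grouped) the factor is D = 1 + (m − 1)ρ. For CogniFit vs treatment as usual (one arm grouped) it is (D + 1)/2.

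**Step 3. True error if the grouping is ignored.** True two-sided error = 2 × [1 − Φ(z/√factor)]. Both levels are shown because the sample size section uses 1.274% and the data analysis section uses 5%.

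| ρ (assumed) | Contrast | Factor | Nominal 5% | Nominal 1.274% |
|---|---|---|---|---|
| 0.02 | vs SIMS 4 | 1.070 | 5.8% | 1.6% |
| 0.05 | vs SIMS 4 | 1.175 | 7.1% | 2.2% |
| 0.10 | vs SIMS 4 | 1.350 | 9.2% | 3.2% |
| 0.02 | vs usual care | 1.035 | 5.4% | 1.4% |
| 0.05 | vs usual care | 1.0875 | 6.0% | 1.7% |
| 0.10 | vs usual care | 1.175 | 7.1% | 2.2% |

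Worked example, ρ = 0.02 vs SIMS 4: 1.960/√1.07 = 1.895, and 2 × [1 − Φ(1.895)] = 5.8%.

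**Step 4. Power of a test that allows for the grouping.** At 66 per arm and the 1.274% level, power = Φ(0.58/√(2 × factor/66) − 2.491). Without grouping it is 0.80. For ρ of 0.02, 0.05 and 0.10 it is 0.77, 0.72 and 0.65 against SIMS 4, and 0.78, 0.76 and 0.72 against treatment as usual.

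**Step 5. The opposite assumption.** Suppose each training group holds equal numbers of CogniFit and SIMS 4 players. The shared effect then cancels between them, and the factor for that contrast is 1 − ρ. At ρ of 0.02 to 0.10, a nominal 5% test has a true error of 2 × [1 − Φ(1.960/√(1 − ρ))] = 4.8% to 3.9%, which is slightly conservative.

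**The case against.** The strongest reply is that this is individual training that happens to be co-located. Each person plays on a separate computer, CogniFit content is fitted to the individual, exercises are largely self-chosen, and the RA helps as needed. Tailored schedules may also change who sits with whom. All of this stands. It points to the lower end of the range, and at ρ = 0.02 the effect is modest. It does not make the correlation zero.

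Second, nothing says that a session contains one arm only. This stands too: under Step 5 the inflation for CogniFit vs SIMS 4 disappears. A reader might take 9.2% as the trial's actual error rate; the article supports neither the correlation nor the group composition behind it.

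Third, the model text is permissive, it allows for other confounders, and an unseen analysis plan may add terms. That is fair as to what may be added later. But the levels are stated outright as two, so the point about training groups does not rest on silence.

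Fourth, a reader might infer that randomisation is wrongly unstratified and that site differences therefore bias the comparison. The documents do not support this. The article gives the list, block size and ratio and is merely silent on strata, which the full protocol may define. Even without strata, chance imbalance between sites is not bias. The article gives no site numbers or sizes, so the extent of any imbalance cannot be computed from it.

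**Conclusion.** The point holds as a weakness of the stated primary model. Delivery in RA-monitored groups, outcome collection by the same RAs, the two-level structure and the independence-based sample size are all in the article.

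The size is uncertain. Under the assumptions in Step 2, true error at a nominal 5% is 5.8% to 9.2% for CogniFit vs SIMS 4 and 5.4% to 7.1% for CogniFit vs treatment as usual, with the lower ends more plausible. For the first contrast the inflation vanishes if groups mix the gaming arms. This is a worthwhile and inexpensive improvement. It does not show that the trial's conclusions would be wrong, and it is not a fault in the randomisation.

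**What to change.** - **Record now.** Recruitment is described as ongoing. For each participant, record the site, the training group, the supervising RA and the RA who assessed each follow-up. Gaming sessions are already logged, so this adds an identifier to an existing record. It also shows whether groups were stable and whether they mixed arms, which settles the main unknowns above.
- **Fixed part of the model.** Add site and site-by-time, so that the adjustment reaches the change contrasts.
- **Random part.** Add a random effect for training group (or for RA) on the post-baseline visits of the CogniFit and SIMS 4 arms only, that is, a partially nested model. Put it in the primary model, or at least in a prespecified sensitivity analysis.

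The cost is one extra identifier, a few model terms and slightly wider confidence intervals. If the correlation proves material, power is below 0.80, as in Step 4. The grouped delivery causes that loss; the added term only makes it visible. The fix needs no extra patients or staff and no change to the allocation scheme.

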#### Treatment as usual (a passive control group)

No specific gaming intervention will be offered to those who receive treatment as usual. To minimise the risk of intervention contamination, the participants will be encouraged not to play video games during the study period and will be asked to report any video gaming with which they may have engaged.

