### Ethical issues

The WMA Declaration of Helsinki [56] and its ethical principles for medical research involving human subjects has guided our study design and protocol. The data collection will be voluntary based; written informed consent forms will be signed by patients. Prior to enrolment, participants will be made aware of all potential risks and benefits of participation (oral and written information). All steps will be taken to avoid any harm to participants. First, to minimise extra burden due to gaming interventions, playing intensity will be set at a maximum of 5 h per week, or it will be tailored to participants’ individual needs. Second, we have chosen video games that are purely fictional and do not include intentional violence. Third, possible changes in a patient’s health status will be continually monitored throughout the project. Fourth, players in this study will play the game under supervision only. Fifth, patients’ participation may be biased toward those who are interested in gaming, which will be taken into account in the conclusions. Any extra costs to the patients as a result of participation (treatment or travel costs, gaming licenses) will be covered.

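### The only side-effect tool described is a diary tied to gaming sessions, so side effects cannot be compared with treatment as usual, nor followed after gaming stops or in months 3 to 6

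*Protocol article*

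**What the plan says.** Interventions gives the route for unwanted effects of gaming, with tired eyes as its example: "feedback and any concerns will be reported in a gaming diary after each gaming session". The same section has a research assistant overseeing the sessions.

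The treatment-as-usual section states "No specific gaming intervention will be offered to those who receive treatment as usual". That arm is asked to avoid video games and "will be asked to report any video gaming with which they may have engaged". It is not asked about health problems.

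Data collection and follow-up, with Table 1, sets the schedule. The depression scale (CDS-C) and the movement scales (SAS, BARS, AIMS) belong to the preparatory stage, which happens once. The cognitive tests, BSPS, TEPS, GSE and CAINS are taken at baseline, 3 months and 6 months, with no restriction by arm.

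Ethical issues lists, among the steps against harm, that "possible changes in a patient’s health status will be continually monitored throughout the project". It names no instrument, schedule or responsible role.

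**The concern.** A diary triggered by a session ascertains side effects differently by arm, and it falls silent when a participant stops playing. If someone stops because gaming made them unwell, what happens next is not recorded by this tool. Tired eyes or fatigue would be noted where gaming takes place, with no background rate from usual care to set beside them.

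This matters because the trial is built to compare cognitive training with both an active and a passive control. The Discussion also says that the clinical consequences of gaming for health and well-being should be understood before recommendations go to patients and decision makers. Diary entries can be compared between the two gaming arms while sessions continue, but not with treatment as usual.

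**Working it through.** The plan states no figure for harm coverage, so there is none to reproduce. The check sets the sections side by side and then sizes the gap.

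**1. What each described source can show**

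| Source | Treatment as usual | After gaming stops | Months 3 to 6 | Eye strain, fatigue, admission, reason for stopping |
|---|---|---|---|---|
| Gaming diary (Interventions) | No | No | No | Side effects and concerns, while sessions last |
| Session supervision (Interventions) | No | No | No | No separate record described |
| CDS-C, SAS, BARS, AIMS (Table 1) | Before allocation only | No | No | No |
| CAINS, BSPS, TEPS, GSE, cognitive tests (Table 1) | Yes | Yes, if the visit is attended | Yes, at 6 months | No |
| Health monitoring (Ethical issues) | Not limited by arm | Not limited | Not limited | No method stated |

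The one source with both a method and a side-effect purpose is the diary, and its first three cells are empty. The one source broad enough to fill them has no method.

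**2. Inputs for the size**

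- 78 per arm, 234 in total (Interventions). Power analysis and sample size gives 79 and 237.
- A 12-week intervention (Recruitment), taken here as 3 months.
- Follow-up to 6 months after baseline (Data collection and follow-up).
- 16% drop-out during the intervention (Power analysis and sample size).

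**3. Participants with no diary by design**

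78/234 = 33.3%. Using 79/237 gives the same share.

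**4. Planned person-time under the diary**

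- Total: 234 x 6 = 1404 person-months.
- Gaming arms during the intervention: 156 x 3 = 468.
- Coverage with no drop-out: 468/1404 = 33.3%.

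**5. With drop-out, keeping planned follow-up as denominator**

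- Expected drop-outs in the gaming arms: 0.16 x 156 = 25, leaving 131.
- Leaving on average at 1.5 months: (131 x 3 + 25 x 1.5)/1404 = 430.5/1404 = 30.7%.
- All leaving at once: (131 x 3)/1404 = 393/1404 = 28.0%.

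**6. With drop-outs removed from the denominator as well**

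- Person-time in each half with no drop-out: 234 x 3 = 702.
- Leaving evenly in the first half: 702 x 0.92 + 702 x 0.84 = 1235.5.
- Diary time: 468 x 0.92 = 430.6.
- Coverage: 430.6/1235.5 = 34.9%.

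The share thus lies between 28.0% and 34.9%, depending on the drop-out assumption and the denominator. It measures how much follow-up the tool can reach. It does not measure harm missed, because most of the uncovered time has no gaming scheduled.

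**The case against.** The strongest reply is that the diary suits its purpose. It records effects of gaming sessions, and against that purpose it covers every session attended. The objectives and hypotheses contain no safety question, and no between-arm harm comparison is promised. This stands in part: the diary is not a mistake, and the person-time share should not be read as a failure rate. But without a common source the trial cannot say whether a complaint is more frequent with gaming than without it.

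Three stronger readings are tempting, and the article does not support them.

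- *That there will be no harm data outside the diary.* CAINS, BSPS and the cognitive tests are repeated in every arm at 3 and 6 months, and worsening could show there. They are efficacy outcomes, however, and do not capture the items at issue.
- *That drop-outs contribute nothing.* They complete diaries until they stop, and only the time afterwards is uncovered. Under Trial design, the diaries also confirm the number of drop-outs, although no reason for stopping is mentioned.
- *That the monitoring promise is broken, or contradicts the diary rule.* Both statements can be followed together, and a journal article condenses a fuller protocol that is not shown and may hold adverse-event procedures. The text shows a commitment without a described method, and no more.

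What remains does not rest on silence alone: the article states a tool, its trigger and an instrument schedule, and together these make side-effect collection depend on arm.

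**Conclusion.** The point holds in a limited form. As described, side-effect data come from a session-linked diary. They are absent for one third of participants by design, for the gaming arms once a participant stops, and for everyone in months 3 to 6. Scheduled instruments at follow-up do not fill the gap, and the wider monitoring commitment has no stated method. Side effects therefore cannot be compared with usual care.

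This rests on the article being complete about its side-effect tool and Table 1. If the full protocol collects adverse events in all arms, the point reduces to making the article say so. It does not affect the primary efficacy analysis. It is an improvement worth making, at modest cost, while recruitment continues.

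**What to change.** 1. Keep the diary as a session log for the gaming arms, and report its content as description of those arms.
2. Add one short, structured question set, identical in all three arms, at the existing 3- and 6-month visits. It should ask about new or worsened health problems, admissions and, where relevant, the reason for stopping gaming. Include participants who have stopped.
3. Base any between-arm description of harms on that set. State two limits: the research assistants who collect follow-up data are not masked (Randomisation, allocation concealment and blinding), so reporting may differ by arm, and participants already past a visit will be missed.
4. Use medical records to check admissions only where consent allows. The article has clinical staff screen records for privacy reasons, and the research uses it states are IQ and medication dosage at the preparatory stage.
5. Reconcile Interventions, Data collection and follow-up (with Table 1) and Ethical issues, so that the monitoring commitment names what is collected, when and by whom.

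The cost is a wording change and slightly longer visits, with no additional visit. Any use of records beyond present consent would need further consent wording.
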